## Abstract

**Background:** Impairment of upper limb function following stroke is more common than lower limb impairment and is also more resistant to treatment. Several lab-based studies with stroke patients have produced statistically significant gains in upper limb function when using musical instrument playing and techniques where rhythm acts as an external time-keeper for the priming and timing of upper limb movements.

**Methods:** For this feasibility study a small sample size of 14 participants (3–60 months post stroke) has been determined through clinical discussion between the researcher and study host in order to test for management, feasibility and effects, before planning a larger trial determined through power analysis. A cross-over design with five repeated measures will be used, whereby participants will be randomized into either a treatment (*n* = 7) or wait list control (*n* = 7) group. Intervention will take place twice weekly over 6 weeks. The ARAT and 9HPT will be used to measure for quantitative gains in arm function and finger dexterity, pre/post treatment interviews will serve to investigate treatment compliance and tolerance. A lab based EEG case comparison study will be undertaken to explore audio-motor coupling, brain connectivity and neural reorganization with this intervention, as evidenced in similar studies.

**Discussion:** Before evaluating the effectiveness of a home-based intervention in a larger scale study, it is important to assess whether implementation of the trial methodology is feasible. This study investigates the feasibility, efficacy and patient experience of a music therapy treatment protocol comprising a chart of 12 different instrumental exercises and variations, which aims at promoting measurable changes in upper limb function in hemiparetic stroke patients. The study proposes to examine several new aspects including home-based treatment and dosage, and will provide data on recruitment, adherence and variability of outcomes.

## Background

There are approximately 152,000 people affected by stroke in the UK every year (British Heart Foundation, 2012) causing more disability in adults than any other disease or condition. More than 50% of these report severe disability (Adamson et al., 2004b) and face long-term dependency on others for support with daily activities in their home (Adamson et al., 2004a). The mean length of stay in hospital for stroke patients in the UK has fallen from 32 days in 2000 to 20 days in 2010 (British Heart Foundation, 2012). Community services, sometimes referred to as “early supported discharge teams,” and other community based rehabilitation teams are reported to improve outcomes for stroke patients, but an audit in 2010 recorded only 36% of hospitals in the UK were providing such services (Department of Health, 2010). A shortfall in spending on chronic stroke rehabilitation is also reported in the US (Miller et al., 2010), despite the fact that studies have shown improvements in outcomes for patients when interventions continue from acute care into the community up to five years after stroke (Fens et al., 2013).

Weakness on one side, or hemiparesis, is the most commonly encountered sensorimotor impairment following ischaemic or haemorrhagic stroke (Sabini et al., 2013), occurring in 80% of patients (Adey-Wakeling and Crotty, 2013). Hemiparesis has a profound effect on patients' ability to perform ADLs such as washing, dressing, cooking and eating, and is extremely resistant to rehabilitation treatments. The total financial costs resulting from stroke in 2009, including direct health care costs, productivity loss and informal care were £3,741,682 (British Heart Foundation, 2012). Other estimates put the annual cost figure at 7 billion with 2.8 billion comprising direct healthcare costs (Bhatnagar et al., 2010).

Research beginning in the 1990s into rhythm driven interventions for gait training following stroke and traumatic brain injury (Thaut et al., 1993, 1997, 2007; Prassas et al., 1997; Hurt et al., 1998), in Parkinson's disease (Thaut et al., 1996; McIntosh et al., 1997), and with cerebral palsy (Kwak, 2007; Kim et al., 2011, 2012) has resulted in a well evidenced intervention known as Rhythmic Auditory Stimulation (RAS). RAS is reported to improve gait parameters including stride length and symmetry with stroke patients, with further research recommended into rhythm driven interventions in neurorehabilitation (Bradt et al., 2010). Building on this research Thaut et al. (2002) and Malcolm et al. (2009a) found evidence for the application of rhythm driven interventions in upper limb rehabilitation, with participants making significant improvements in movement trajectories and quality of arm movement. Motivation is a major factor that, when lacking, can hinder engagement in rehabilitation programs, and a number of other studies illustrate the use of music and the inclusion of music therapy within multidisciplinary rehabilitation in order to improve patient mood and enhance motivation (Nayak et al., 2000; Jochims, 2004; Magee et al., 2006; Craig, 2008; Sarkamo et al., 2008; Magee and Baker, 2009; Street, 2012). Using electronic drums supported with live music from the music therapist, Paul and Ramsey (1998) found clinical (but not statistical) significance in increased active shoulder and elbow range for stroke participants. Sharing some features with this study, Music Supported Therapy (MST) is a recently researched intervention in which participants played through a series of increasingly complex musical exercises using electronic drum pads and keyboard. Results from these studies have consistently shown statistically significant improvements for participants' upper limb function, also evidencing neural reorganization using EEG and fMRI technology (Schneider et al., 2007; Rojo et al., 2011; Altenmüller et al., 2009; Grau-Sánchez et al., 2013). EEG was recorded during playing, i.e., hitting a key or a drum pad, which would indicate an event in the EEG. Pre-post therapy results in the music group showed an increase of Event-Related-Desynchronization and coherence in the beta band indicating reorganization of motor patterns (Altenmüller et al., 2009). Rojo et al.'s case study indicated that music patterns that were listened to before they were played by participants showed increased activation of motor and auditory regions when listening after the patterns had been learned, at the end of treatment (Rojo et al., 2011). Evidence suggesting that the music generated by the participants' playing during these studies has induced neural reorganization, whereby the auditory cortices appear to be incorporated into motor circuits, has prompted use of the term “audio-motor coupling” (Rojo et al., 2011), a phenomenon also observed within minutes of novice piano players beginning to practice (Classen et al., 1998). Musical motor performance involves the same brain regions as other motor tasks, those being the: motor, premotor, supplementary motor area (SMA), the cerebellum and the basal ganglia, as well as somatosensory, auditory, emotional, temporal, and memory loops (Altenmüller, 2001; Lotze et al., 2003; Meister et al., 2004). Musicians perform complex movement patterns, which are informed by continuous auditory feedback from their playing (Altenmüller et al., 2009), and feedback from movements is fundamentally important in order to inform and control them (Carpenter and Reddi, 2012).

Therapeutic Instrumental Music Performance (TIMP) is a Neurologic Music Therapy intervention (NMT) used in neurorehabilitation which employs external audio cues during music based activities in which the selection and spatial arrangement of instruments facilitates improved upper limb movement trajectories and arm kinematics (Thaut, 2008). Jeong and Kim (2007) suggest that the combination of rhythmic music and movement attuned to it creates a powerful neurological stimulus that may increase the plasticity of the nervous system. TIMP is one of a number of NMT interventions applied to sensorimotor, cognitive and communication rehabilitation (Thaut, 2008). It involves the planning of functional therapeutic musical experiences to meet functional physical goals, set within the multidisciplinary team, with the aim of transferring the therapeutic learning into real-world applications. Whilst evidence has emerged from the aforementioned studies regarding the effects of either rhythm or musical instrument playing on neural reorganization and upper limb movement trajectories, there have been very few that combine these elements to form a unified treatment protocol matching that of TIMP. Lim et al. (2011) investigated its effects on perceived exertion and fatigue, with positive findings, but did not measure for any physiological change. Paul and Ramsey's (1998) study matches the TIMP protocol, but was delivered in a group setting. Yoo (2009) conducted a study using TIMP in a lab setting with three chronic stroke patients and found evidence of improved wrist and hand function, as well as increased movement velocity.

Music therapy is not commonly associated with, nor found within, neurorehabilitation settings; in 2005 only four neurorehabilitation units in the UK employed a music therapist (Magee et al., 2006). Musical instrument playing is not widely recognized as a feasible and effective, short-term intervention for treating movement disorders resulting from stroke, a patient group within which there is a high level of heterogeneity as regards upper limb hemiparesis, cognitive, sensory and communication impairments. Yoo's study, which included three participants, was conducted at Colorado State University, a major center for NMT research and training. Participants were recruited from a facility managed by their center for biomedical research in music. Heterogeneity influences decisions regarding inclusion criteria; if it is too specific, then recruitment can be slow, too broad and heterogeneity introduces more variables, which in turn may skew statistical outcomes. In either case, a further influence is the pool size from which patients will be recruited; the geographical area and whether single or multi-site.

Home based and combined home/clinic training programs for sensorimotor treatment have been trialed previously using RAS gait training with Parkinson's patients (Thaut et al., 1996), rhythmic auditory cueing for upper limb reaching kinematics with stroke patients (Malcolm et al., 2009b), and computer gaming (King et al., 2012), however, all other research relating to this topic has been laboratory based. There is a lack of research investigating sensorimotor interventions with patients at the home-based community stage of rehabilitation. Previous studies investigating musical instrument playing have included in-patients, who were, on average, approximately 2 months post-stroke (Schneider et al., 2007; Altenmüller et al., 2009; Grau-Sánchez et al., 2013). One study using a rhythm and music-based therapy program included participants at 1–5 years post stroke (Bunketorp Kall et al., 2012). This study will include participants 3–60 months post stroke, defined as being at the chronic stage of recovery (Barrett and Meschia, 2013).

Frequency of therapy sessions in existing studies has been predominantly 5 days per week for 3–4 weeks (Schneider et al., 2007; Altenmüller et al., 2009; Malcolm et al., 2009a; Rojo et al., 2011; Amengual et al., 2013), which is comparable with typical modified constraint induced movement therapy (mCIMT) delivery (Earley et al., 2010), and the music therapy treatment has usually been compared with other forms of standard care or combined music therapy/standard care. Early versus late treatment using RAS in gait training has been trialed (Hayden et al., 2009), but music therapy treatment for upper limb rehabilitation has not been investigated using a wait list design. The feasibility of delivering RAS for stroke patients as part of standard care has been explored (Hayden et al., 2009). Owing to the innovative nature of this intervention and recruitment of participants from within an NHS trust where neurologic music therapy is not recognized or available, participants will be recruited after discharge from community stroke rehabilitation services.

The study reported here will build upon the existing knowledge of music's effect on neuroplasticity (Schneider et al., 2007; Altenmüller et al., 2009; Rojo et al., 2011; Amengual et al., 2013) and translate this knowledge into a clinical protocol that may improve patient outcomes. Thus, it will add to limited, existing research into musical instrument playing, rhythm and upper limb rehabilitation following stroke. It will also address questions concerning dosage, setting and the timing of treatment delivery. Whereas most of the research to date on this topic has been laboratory based, this study provides a novel intervention that will be delivered one-to-one, in participants' homes. It will therefore examine the feasibility of home treatment delivery at the end of standard community care. In addition, participant experience of TIMP recorded via semi-structured interview will provide data regarding motivation, access and compliance to treatment. Frequency of sessions will be reduced compared to previous studies, in order to determine whether it is still effective at a lower dosage and to ensure that the sample size can be treated within the timeframes and resources available for this research.

### Study aims and objectives

The aims of this crossover study are to investigate whether TIMP is a feasible and effective home-based intervention for upper limb hemiparesis following stroke, when delivered at a frequency of twice weekly for a period of 6 weeks. Additional qualitative data gathered will explore the participant experience of this treatment with specific focus on feasibility of treatment delivery in the home, patient motivation, and patient preference with regard to the treatment methods under investigation. This biomedical research study is registered with clinical trials.gov, number NCT 02310438 and also approved by the Integrated Research Application System (IRAS) and Anglia Ruskin University Ethics Boards.

## Methods

### Study design

A cross-over design with repeated measures will be used, with participants being randomized into either a wait list or treatment group (see Figure 1). Assessments for each participant will take place at the same time points after baseline measure, as illustrated in Figure 1, with the baseline and end assessments immediately before and after the 6 weeks of TIMP being conducted by a therapist who is blind to participant allocation.

**Figure 1 F1:**
[figure not shown]
**Study consort, showing the crossover design with repeated measures**. BA, Blind Assessor, who will conduct ARAT and 9HPT indicated at Weeks 1 and 6 (treatment), 9 and 15 (wait list).

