### Procedure

Each participant will have a total of 12 individual music therapy sessions in their home, delivered twice weekly over the course of 6 weeks. They will not be required to perform any practice or exercises set by the researcher between sessions. Whilst in wait list, before the intervention begins, participants will not receive any community nor privately employed rehabilitation interventions for upper limb hemiparesis. Each participant will also receive the Action Research Arm Test (ARAT) (Lyle, 1981) and Nine Hole Peg Test (9HPT) (Kellor et al., 1971) assessments at the same five time points after baseline measure, over an 18 week period as follows: Timepoint 1 at Week 1 after randomization; timepoint 2 at week 6; timepoint 3 at week 9; timepoint 4 at week 15; and timepoint 5 at week 18. The design will allow analysis of treatment and no treatment by comparing treatment group with wait list group data. It will also be possible to compare early versus late intervention following discharge from the community rehabilitation treatment, as the wait list participants will have a delay of 9 weeks between community discharge and beginning TIMP. Data collected from wait list group participants prior to TIMP treatment will be analyzed to determine whether there has been any spontaneous change in upper limb function, which can occur as an independent covariate (Kwakkel et al., 2006). Subject data from the ARAT and 9HPT will also be individually analyzed in order to discuss group results.

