### Participants

Fourteen adult participants, 3–60 months post stroke, with hemiparesis will be recruited who have been discharged from community rehabilitation and can consent to treatment. The age range for inclusion will be 18–90. As with the MST studies (Schneider et al., 2007; Altenmüller et al., 2009; Rojo et al., 2011; Amengual et al., 2013) participants must be able to lift their affected hand up on to a table whilst seated, unaided by their unaffected side and have some finger movement in the affected hand. In a meta-analysis of literature reporting prognostic variables in upper limb recovery (Coupar et al., 2012), inconclusive evidence was found for time since stroke being a predictor. Comparisons between lesion site also revealed no predictive value in upper limb recovery. The most significant findings were that patients recovered significantly more upper limb function if there was less impairment in their upper limb initially caused by the stroke. The inclusion criteria for this feasibility study has been determined based on this research and that set for the MST studies earlier cited. On entry into the study participants will be randomized to either the treatment or wait list group, with a list of numbers randomly generated by an independent statistician using a computer, which will be concealed using opaque sealed envelopes. The assessor will be blinded to participant allocation. In order to maintain blinding the researcher will deliver a script for all participants and the assessor at each assessment time-point.

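### The blind assessor is assigned only to the visits around each arm's own TIMP course, so the randomised Week 1 to 6 comparison has a named blind rater in one arm only

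*Protocol article*

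**What the plan says.** All references are to the protocol article, Methods.

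- **Procedure.** Every participant has ARAT and 9HPT "assessments at the same five time points after baseline measure, over an 18 week period as follows: Timepoint 1 at Week 1 after randomization", then "timepoint 2 at week 6; timepoint 3 at week 9; timepoint 4 at week 15; and timepoint 5 at week 18". The treatment effect is to come from a between-group comparison: "The design will allow analysis of treatment and no treatment by comparing treatment group with wait list group data".
- **Figure 1 legend.** The blinded ratings are allotted by arm and week: "BA, Blind Assessor, who will conduct ARAT and 9HPT indicated at Weeks 1 and 6 (treatment), 9 and 15 (wait list").
- **Study design.** The text ties blinded rating to each participant's own treatment course: "immediately before and after the 6 weeks of TIMP being conducted by a therapist who is blind to participant allocation".
- **Participants.** Blinding is stated without limit to particular visits: "The assessor will be blinded to participant allocation". The safeguard is also general: "In order to maintain blinding the researcher will deliver a script for all participants and the assessor at each assessment time-point".
- **Measures.** ARAT is the primary outcome.
- **Statistical analysis.** A linear mixed model is planned, and its main result is to be whether the therapy had an effect.

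**The concern.** Blinded rating protects a treatment comparison when it applies alike to both arms. Here it follows the treatment course, and the course falls at different weeks in the two arms. Between Weeks 1 and 6 one arm receives TIMP and the other is still untreated. That is the period in which randomisation supports a causal reading, and only the treatment arm has a named blind rater in it.

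ARAT is administered and scored by an observer. A rater who knows that a participant is still waiting may score, or encourage, differently from a rater who does not know. Such a bias would be read as a treatment effect, and analysis could not reliably separate the two afterwards.

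Two further consequences follow. First, blind-assessor status changes between Weeks 6 and 9 in both arms, in opposite directions. If raters differ in level, this disturbs the reading of retention in the treatment arm and of spontaneous change before TIMP in the wait list. Second, the assessor meets each participant once before and once after that person's TIMP. The second meeting is always post-treatment, so treatment status is not masked even if allocation is.

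**Working it through.** **Inputs.** 7 participants per arm (Abstract); five common time points (Procedure); blind-assessor visits by arm and week (Figure 1 legend, confirmed by Study design). The plan gives no figure of its own to reproduce, and the sample size of 14 does not come from a power calculation (Sample size).

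**Step 1: blind assessor named, by arm and week.**

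| Week | Treatment | Wait list |
|---|---|---|
| 1 | yes | no |
| 6 | yes | no |
| 9 | no | yes |
| 15 | no | yes |
| 18 | no | no |

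- Planned assessments: 14 × 5 = 70.
- With a named blind rater: 7 × 2 + 7 × 2 = 28, and 28/70 = 40%. The other 70 − 28 = 42 have no named rater.
- Blind status coincides with arm at Weeks 1, 6, 9 and 15, that is 4 of 5. Time points with both arms blind: 0 of 5.

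**Step 2: a constant rater offset.** Suppose the blind assessor scores b ARAT points higher than the other rater, at every visit and in every participant.

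| Contrast | Shift |
|---|---|
| Week 6 difference, treatment minus wait list | b − 0 = +b |
| Week 15 difference, treatment minus wait list | 0 − b = −b |
| Arm difference in Week 1 to 6 change | (b − b) − (0 − 0) = 0 |
| Arm difference in Week 9 to 15 change | 0 |
| Treatment arm, Week 6 to 9 change | 0 − b = −b |
| Wait list, Week 6 to 9 change | b − 0 = +b |
| Wait list, Week 15 to 18 change | 0 − b = −b |

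In least squares with participant and time-point effects on complete data, the shift in the treatment effect is 0 if the effect is coded as lasting after TIMP. It is 1.0 × b if the effect is coded only at the end-of-TIMP visit.

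**Step 3: expectation bias that varies by visit.** Let e1 and e6 be the bias in the wait-list ratings at Weeks 1 and 6. The arm difference in Week 1 to 6 change then shifts by −(e6 − e1). This is zero only if the bias is the same at both visits. If wait-list participants are scored c points too low at Week 6 and correctly at Week 1, the estimated benefit rises by the full c. The document gives no basis for a value of b or c, so none is assumed.

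**Step 4: what the assessor can infer.** If the assessor knows the study week and the schedule, a visit at Week 1 or 6 means treatment with probability 1, and a visit at Week 9 or 15 means wait list with probability 1, against 0.5 by chance. If the assessor does not know the week, the two arms present the same sequence, one visit before TIMP and one after. The arm then cannot be read from the visits, but before-or-after status can.

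**The case against.** Several points on the other side are fair.

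- **The design may look worse than it is.** A reader might infer that blinding is confounded with arm throughout. It is not: at Week 18 neither arm has a named blind rater, which is absence of blinding and not confounding.
- **Allocation is not necessarily revealed.** A reader might infer that the visit week gives the arm away and that no script could prevent it. That holds only if the assessor knows the study week or schedule. The article does not say what the assessor is told, nor what the script contains. If entry is staggered, a calendar date alone would not show the week.
- **The other raters are not described.** A reader might infer that the treating researcher, or someone else known to be unblinded, does the remaining 42 assessments. The article names nobody for them. The supported statement is that no blind rater is named.
- **Rater differences may be small.** Measures reports excellent inter-rater reliability for ARAT and a standard table map, and a constant offset cancels in the Week 1 to 6 change. This limits b but does not bear on expectation bias.
- **It is a feasibility study.** It has 14 participants, no power calculation, and a Discussion that does not predict significant group results. Yet effectiveness is among its aims, the analysis section makes the treatment effect the main result, and the study is meant to prepare a larger trial.
- **An article condenses.** The full protocol may name the other raters. The point does not rest on that omission: two places state which visits the blind assessor covers, and the Participants section does not match them.

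**Conclusion.** The concern holds in this limited form. By the plan's own allocation of visits, 28 of 70 assessments have a named blind rater, blind rating coincides with arm at 4 of 5 time points, and both arms are never blind-rated together. In the Week 1 to 6 comparison, differential expectation bias in the primary outcome would pass one-for-one into the estimated effect. A constant rater offset would not bias that change contrast. It would bias the Week 6 difference by b and the Week 6 to 9 change by −b in the treatment arm and +b in the wait list.

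The conclusion rests on the Figure 1 legend and the Study design text, since the figure itself was not available to this review. It also takes it that the visits without a named blind rater are not in fact blinded by the same assessor. If they are, the legend and the Study design text are wrong and need correcting. Either way, those two places and the Participants section must be reconciled. The size of any bias cannot be given from the document.

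**What to change.** 1. **Minimum change.** Have the blind assessor rate all 14 participants at Week 1 and at Week 6: 14 × 2 = 28 visits, the number already planned. This makes the randomised contrast symmetric with no extra visits. The second visit also stops implying that TIMP has been given. The downside is that the wait-list ratings at Weeks 9 and 15 lose the blind assessor.
2. **If the same assessor's time allows.** Cover both arms at Weeks 9 and 15 as well: 14 × 4 = 56 visits, 28 more than planned. At the stated maximum of 30 minutes per ARAT this is up to 28 × 0.5 = 14 hours, plus 9HPT and travel time across three geographically separate teams.
3. **Masking.** Keep the assessor unaware of study week and of earlier scores, and say so in the plan.
4. **Text.** Align Study design, the Figure 1 legend and Participants, and state who carries out the remaining visits and whether they are blinded.
5. **Analysis.** Do not add a rater-type term. Under item 1, rater type is fixed by time point (blind at Weeks 1 and 6, otherwise not). Under item 2 it only separates Week 18 from the rest. In both cases it is aliased with categorical time and cannot be estimated.
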